#### Muscle adaptation

A needle biopsy of the vastus lateralis, performed as described by Bergström and routinely done in our laboratory will be obtained before and after the 8-week intervention to investigate muscle adaptation to training (key proteins of IGF-1/PI3/AKT pathway, FOXOs, MuRF and MABx/atrogin, fiber-type distribution, enzymatic activities and capillarization).

#### Quality of life and feasibility

Quality of life will be determined with the COPD Assessment test (CAT) [42] and the feasibility of the exercise regimens will be assessed by compliance (number of attended training session) and progression of intensity. The occurrence and severity of any adverse events will be recorded.

### Randomization and blinding

To prevent foreknowledge of treatment assignment and to keep the allocation sequence concealed from the participants and the researchers, group allocation will be done after the completion of baseline and inclusion tests by an individual independent of the recruitment process using a randomly permuted blocks design with a computer random number generator. Randomization will be performed with a 1:1 allocation to the intervention or control group. The allocation sequence will be kept in an opaque, sealed and stapled envelope and will be kept concealed until end of outcome assessment. The envelope will be made impermeable to intense light by using aluminum foil inside and sealed using tamper-proof labels. Furthermore, the participants will be given repeated instructions not to reveal their group allocation to the outcome assessors. In case of failure in keeping the outcome assessor blinded (that is, a patient reveals his/her group allocation), a second trained outcome assessor will be available.

### Statistics

The analysis of primary and secondary outcome measurements will include all randomized patients analyzed by their original group in accordance with intention-to-treat. Within group and between group changes will be analyzed using linear mixed models. In addition, within the main analysis, an on-treatment analysis will be performed. On-treatment is defined as at least 75% compliance, in other words at least 18 training sessions. Mixed models will be used to handle missing outcome data. For comparison of single and two limb exercises student t-tests will be performed. A level of 0.05 will be considered valid for statistical significance. For data management and statistical analysis the IBM Statistical package for Social Science (SPSS) version 21.0 will be used.

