### Hypotheses

The following hypotheses are proposed:Single-limb high-repetitive resistance training will provide a larger gain in the 6-min walking distance than the two-limb high-repetitive resistance training in patients with severe to very severe (stage 3 to 4) COPD.Eight weeks of single limb high-repetitive resistance training will be associated with larger physiological (muscle endurance, fatigue and deoxygenation) and structural (muscle protein synthesis, fiber-type distribution and capillarization) adaptations to training, and lower cardiorespiratory demand, as well a greater increase in health-related quality-of-life in comparison to two-limb high-repetitive resistance training.Two-limb high-repetitive resistance training will lead to larger restraints on the ventilatory system and higher dyspnea scores and, to reduced muscle fatigue, deoxygenation and localized exercise stimulus in comparison to single-limb high-repetitive resistance training in patients with COPD. Healthy controls will be able to train both legs/arms simultaneously without central constraints and with no differences in muscle fatigue or exercise stimulus between the two high-repetitive regimens.

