### Sample size and eligibility criteria

A total of 30 patients will be included. This sample size was calculated with the premises that 13 patients in each group would be required to obtain sufficient power to detect a 34-m (±30) between-group difference in the 6-minute walk test (6MWT), α = 0.05, β = 0.20 (80% power), and a two-tailed test of significance, based on the previous study on high-repetitive resistance training in COPD [14]. We are aiming to detect at least a 30-m difference between the two groups since this value is considered to be clinically significant in this population [21]. Considering a 15% drop-out rate in this type of study, a total of 30 patients will be recruited. In addition, for the acute phase of this protocol, a sample size of 11 patients with COPD and 11 controls is required to detect a relevant mean difference of 11% (±9) in limb muscle contractile fatigue between single-limb and two-limb execution of the exercises performed in the acute phase of this protocol for an α = 0.05, β = 0.20 (80% power), and a two-tailed test of significance based on a study by Rossman *et al*. comparing single-leg to two-leg knee extension in healthy adults [22].

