### Procedure

Participants will perform three visits for the acute phase of the protocol. These visits are also used as baseline testing for patients with COPD who will contribute to the chronic phase of the protocol. The same evaluation will also be performed after the 8-week training program in patients with COPD. Pre- and post-tests will be performed at similar time of day, with the same rest between test occasions and between tests.

Since a subject’s motivation may determine attainment of maximal effort [5], both pre- and post-tests are performed using standardized information and encouragement [27]. No additional follow-up other than directly after end of intervention period is used within this trial. The perception of dyspnea and muscle fatigue will be measured with the modified Borg scale [28] before and directly after all physical tests as commonly and reliably used in patients with COPD [29,14,30].

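### The acute-phase claim of a mode difference in COPD but none in healthy controls is given only Student t-tests, which cannot show absence in controls or a contrast between the groups

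*Protocol article*

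**What the plan says.** The third hypothesis in the Protocol article (Hypotheses) has two parts. For patients, two-limb training is expected to lead to "reduced muscle fatigue, deoxygenation and localized exercise stimulus in comparison to single-limb high-repetitive resistance training in patients with COPD". Healthy controls are expected to manage both modes without central constraints, "with no differences in muscle fatigue or exercise stimulus between the two high-repetitive regimens".

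The acute phase is sized (Sample size and eligibility criteria) at 11 patients and 11 controls to detect a "mean difference of 11% (±9) in limb muscle contractile fatigue between single-limb and two-limb execution", two-tailed, α = 0.05, 80% power. The figure comes from a study "comparing single-leg to two-leg knee extension in healthy adults".

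For analysis, the Statistics section gives one sentence: "For comparison of single and two limb exercises student t-tests will be performed". The significance level is 0.05. The linear mixed models in that section are for changes within and between groups, in an analysis set of all randomized patients. Controls are not randomized to training, so those models do not cover them.

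Every participant performs both modes, on separate visits (Limb muscle function), in randomized visit order (Table 1 footnote). For patients, "These visits are also used as baseline testing for patients with COPD who will contribute to the chronic phase of the protocol", so up to 30 of them may supply acute data.

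**The concern.** The hypothesis is a pattern across two groups: an effect in one and none in the other. The named method tests for a difference between modes. Applied to patients and controls in turn, it yields two p-values. Nothing in the document says how the second would support absence, or how the two would be compared.

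The tempting summary is that a significant result in COPD and a non-significant one in controls confirms the hypothesis. That pattern arises readily when both groups have the same true difference, because significance also depends on sample size and chance. The acute phase is the only part of the trial with healthy controls, and it is meant to show why single-limb training might suit COPD in particular. If the mechanism is read from two p-values, the conclusion could be wrong about whether it relates to the disease at all.

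**Working it through.** **Inputs.** From the sample size section: difference 11%, SD 9, two-sided α 0.05, power 80%, 11 + 11 participants. Assumed: the SD of within-person differences, a true difference of 5.5% (half of 11%) for illustration, equal SDs in both groups, and normal differences.

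**Step 1: the stated n.** The independent-groups formula n = 2 × [SD × (1.960 + 0.842)/difference]² gives 2 × (9 × 2.802/11)² = 10.5, so 11 per group, as stated. Variants: the independent t version gives 11.6, so 12. A paired t-test with ±9 as the SD of differences gives 7.4, so 8, and with n = 11 has 95% power. The document does not say which was used or what ±9 describes. In every case the calculation is one for detecting a difference.

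**Step 2: range for the SD of differences.** If ±9 is the SD per mode and ρ is the within-person correlation, SD_d = 9 × √(2(1 − ρ)). This gives 6.4 (ρ = 0.75), 9.0 (0.5), 11.0 (0.25) and 12.7 (0). The value 9.0 also covers the reading that ±9 is already the SD of differences.

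**Step 3: controls, true difference 5.5%.** The paired t-test with n = 11 has 10 df, critical value 2.228 and non-centrality 5.5 × √11/SD_d. At SD_d = 9 this is 2.03, giving 45% power and 55% non-significance. The 95% CI half-width there is 2.228 × 9/√11 = 6.05, wider than the 5.5% itself.

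**Step 4: the same 5.5% in both groups.** P(significant in COPD, not in controls) = power in patients × (1 − power in controls). At SD_d = 9: 0.449 × 0.551 = 0.25 with 11 patients, and 0.899 × 0.551 = 0.50 with 30.

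| SD_d | Controls non-significant | COPD-only pattern, 11 v 11 | COPD-only pattern, 30 v 11 |
|---|---|---|---|
| 6.4 | 27% | 20% | 27% |
| 9.0 | 55% | 25% | 50% |
| 11.0 | 68% | 22% | 51% |
| 12.7 | 75% | 19% | 47% |

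The result depends on the assumed effect. If both groups shared the full 11%, the false pattern at 11 v 11 would occur in 0.1%, 4% and 20% of studies at SD_d 6.4, 9 and 12.7.

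**Step 5: what better analyses could deliver.** The mode-by-group contrast is approximated by a two-sample t-test on within-person differences. Equivalence in 11 controls is two one-sided 5% tests, simulated with a true difference of zero.

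| SD_d | Contrast of 11%, 11 v 11 | Contrast of 11%, 30 v 11 | Equivalence ±11% | Equivalence ±5.5% |
|---|---|---|---|---|
| 9.0 | 78% | 92% | 97% | 24% |
| 12.7 | 49% | 67% | 69% | 3% |

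For 80% power at ±5.5%, about 25 controls (SD_d 9) or 48 (SD_d 12.7) would be needed.

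**The case against.** The strongest reply is that the COPD hypothesis is a within-patient contrast, which the named t-test answers, and that no listed objective states a formal comparison of patients with controls. The first part stands: a reader might infer that the COPD hypothesis cannot be tested under this plan, and that is not so. The second stands only in part. The hypothesis sets an effect in one group against none in the other, and its control half has no suitable analysis whether or not a contrast is intended.

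A second reply is that a margin, an interaction term and a visit-order term are usual content for a separate analysis plan. That is fair for the details. But the protocol does name a method here, and the named method does not match the hypothesis.

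Three stronger readings are not supported:

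- A reader might infer from n = 11 matching the independent-groups formula that paired data will be analysed as independent, with wrong standard errors. Student t-tests include the paired form. A paired calculation also gives 11 at 80% power if the SD of differences is about 11.7.
- A reader might see a defect in sizing on 11 patients when up to 30 have acute data. Eleven is a required minimum, and nothing restricts the analysis to 11.
- A reader might call the sizing of controls a flat contradiction, since it takes an 11% difference from healthy adults while predicting none in healthy controls. Sizing so that a relevant difference would be seen if present is reasonable. Some tension remains, but whether that knee-extension study predicts a difference across the six exercises here cannot be judged from the protocol.

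**Conclusion.** The concern holds in limited form. The within-COPD comparison is testable as planned, given a paired test. The statement about healthy controls, and any statement that the effect differs between COPD and health, are not supported by the named analysis.

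The size depends on assumptions that the protocol does not settle. For an SD of differences of 6.4 to 12.7 and a true difference of 5.5%, a non-significant control result is expected in 27% to 75% of studies. A false COPD-only pattern is expected in 19% to 25% (11 v 11) or 27% to 51% (30 v 11); it becomes rarer if the shared difference is larger and the SD small.

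This concerns a secondary, mechanistic hypothesis. The primary outcome, 6-minute walking distance, and its mixed-model analysis are not affected. The change is worth making because it is cheap and protects the interpretation of the acute phase.

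**What to change.** For the acute phase, replace the separate t-tests with a linear mixed model. Use a participant random effect and fixed effects for mode, group, mode by group, and visit order. Include all patients with acute data and the controls. Base any statement that the effect differs between COPD and healthy controls on the mode-by-group contrast and its confidence interval.

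For controls, report the mode difference with its confidence interval and do not conclude no difference from non-significance. If an equivalence claim is wanted, state the margin in advance and require the 90% confidence interval to lie inside it. With 11 controls only a margin near ±11% is workable, and that equals the whole difference the protocol calls relevant. A tighter margin would need more controls.

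State also that the mode comparison is paired, and whether ±9 is the SD per mode or the SD of the differences.

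Cost: a change of analysis wording, with no new measurements. The contrast and the confidence intervals need no extra participants, although power for the contrast is modest if the SD is large. The real price is that the no-difference claim becomes harder to make and may not be reachable with 11 controls.

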### Description of intervention and control groups

Patients with COPD will be randomized to either single or two-limb high-repetitive resistance training. Identical high-repetitive resistance exercise regimen will be used for both interventions, with one exception; the intervention group will perform the exercise regimen using a single limb at a time while the control group will, depending on exercise, perform the training using either both arms or both legs. A total of three sets will be performed for each limb. Training time will be shorter for the two-limb high-repetitive training group in comparison to the single-limb training group. To minimize any confounding effects of different amount of time spent with research staff, the control group will perform a light intensity balance exercise that will compensate for the difference in training time between the two interventions.

Both interventions will be provided on the basis of three sessions per week for 8 weeks. They will be performed under direct supervision, individually or in small groups of 2 to 4 participants. The care provider supervising the training will receive standardized education before the start of intervention consisting of written, oral and visual instructions on how to perform and instruct the exercises used in both high-repetitive protocols.

Before the actual training, there will be a 5-minute warm-up period on a stationary cross-trainer, focusing on muscle groups that will be trained during various exercises, including the latissimus row (m. latissimus dorsi), chest press (m. pectoralis major and m. deltoid anterior), knee extension (m. quadriceps), shoulder flexion (m. deltoid anterior), leg curl (m. hamstrings), elbow flexion (m. biceps brachii) and plantar flexion (mm. triceps surae). All exercises will be performed with elastic bands (Thera-Bands, The Hygenic Corporation [name]) with the exception of plantar flexion that will be executed using a weight-machine (Sport Art Fitness, Woodinville, WA, USA). Extended description of the exercise programs for the single-limb and the two-limb group including detailed including illustrations of start and end positions as well as execution of exercise movement is explained more in detail in the additional files [see Additional file 1 and 2].

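### The stated t-tests of single versus two limb do not test Hypothesis 3's contrast between COPD and healthy controls, and cannot show absence of a difference in controls

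*Protocol article*

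**What the plan says.** The Hypotheses section makes a two-part acute-phase claim. In COPD, two-limb exercise is expected to bring more dyspnea and ventilatory restraint and to reduce muscle fatigue, "deoxygenation and localized exercise stimulus in comparison to single-limb high-repetitive resistance training in patients with COPD". Healthy controls are expected to manage both modes "with no differences in muscle fatigue or exercise stimulus between the two high-repetitive regimens".

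The Statistics section gives one sentence to the comparison of modes: "For comparison of single and two limb exercises student t-tests will be performed". Its significance level is 0.05. The analysis of primary and secondary outcomes there "will include all randomized patients analyzed by their original group in accordance with intention-to-treat", with linear mixed models for changes. Only patients are allocated to training ("Patients with COPD will be randomized to either single or two-limb high-repetitive resistance training"), so the controls fall outside that analysis.

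Under Sample size and eligibility criteria, the text states for the acute phase that "a sample size of 11 patients with COPD and 11 controls is required". The target is given as "a relevant mean difference of 11% (±9) in limb muscle contractile fatigue between single-limb and two-limb execution", at two-sided 0.05 and 80% power. The effect comes from a cited study in healthy adults. The same section plans 30 patients in total. The Procedure section says of the three acute visits: "These visits are also used as baseline testing for patients with COPD who will contribute to the chronic phase of the protocol".

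**The concern.** A claim that an effect is present in one population and absent in another needs two things: an estimate of how much the effect differs between the populations, and a positive demonstration that it is negligible in the second. The stated t-tests supply neither. A difference test can fail to reject simply because the group is small.

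The group sizes may also be unequal. If every patient's acute visits are analysed, there are up to 30 patients against 11 controls, so a paired test in COPD is much more sensitive than the same test in controls. A shared effect of moderate size could then look specific to COPD.

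The planning figures add to the mismatch. The 11-point effect is taken from healthy adults, the population in which the hypothesis predicts no difference in muscle fatigue.

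At stake is the evidence that the advantage of single-limb work is specific to COPD. That comparison is also the controls' role in the study, since they take part only in the acute phase.

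**Working it through.** **Inputs from the protocol article.** Relevant difference 11 points and SD 9 for contractile fatigue, 11 patients and 11 controls, two-sided 0.05, 80% power (Sample size and eligibility criteria); up to 30 patients with acute data (same section, with Procedure); both modes done by each person at two visits (Limb muscle function).

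**Reproducing the plan's figure.** For two independent means, n per group = 2 × (9/11)² × (1.960 + 0.842)² = 10.5, rounded up to 11. The stated size reproduces, with 81.8% power by the normal approximation. The arithmetic is not at fault.

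**What the SD of 9 means.** The text does not say whether 9 is the SD within a condition or of the within-person difference. If it is per condition with correlation ρ between modes, the SD of the difference is 9 × √(2(1 − ρ)): 12.7 at ρ = 0, 9 at ρ = 0.5, 7.0 at ρ = 0.7. These three values are assumptions that span the range.

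**Misleading pattern under an equal true effect.** Let P(n) be the power of a paired t-test with n people, from the noncentral t with n − 1 degrees of freedom and noncentrality effect × √n / SD. The chance of significance in COPD but not in controls is P(n in COPD) × [1 − P(11)].

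| True effect in both groups | SD of difference | P(11) | P(30) | 11 vs 11 | 30 vs 11 |
|---|---|---|---|---|---|
| 5.5 | 7.0 | 0.656 | 0.987 | 22.6% | 34.0% |
| 5.5 | 9 | 0.449 | 0.899 | 24.7% | 49.5% |
| 5.5 | 12.7 | 0.254 | 0.629 | 19.0% | 46.9% |
| 11 | 7.0 | 0.997 | 1.000 | 0.3% | 0.3% |
| 11 | 9 | 0.954 | 1.000 | 4.4% | 4.6% |
| 11 | 12.7 | 0.734 | 0.995 | 19.5% | 26.5% |

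Example: 0.899 × (1 − 0.449) = 0.495. Over all effect sizes the maximum is 25% with 11 per group and about 52% with 30 versus 11.

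**Absence in controls.** A true 5.5-point effect is missed in 11 controls with probability 1 − P(11): 34%, 55% and 75% at SDs of 7.0, 9 and 12.7.

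**Direct contrast.** A two-sample t-test on within-person differences keeps the false-positive rate at 5% when the groups respond alike. At SD 9 its 95% CI half-width is:
- 30 vs 11: 2.023 × 9 × √(1/30 + 1/11) = 6.4 points
- 11 vs 11: 2.086 × 9 × √(2/11) = 8.0 points

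Power for 11 points in COPD against 0 in controls is 92% (30/11) or 78% (11/11) at SD 9, and 67% or 49% at SD 12.7.

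**A margin of 11 points would be too lenient.** With 11 controls, SD 9 and a true effect of 5.5, the 95% CI lies wholly within ±11 about 45% of the time; at SD 7.0, about 66%.

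**The case against.** A reader might infer that the protocol plans separate tests in each group and will treat a non-significant control result as proof of no difference. The text says neither. Its sentence on t-tests does not name the groups, and a t-test comparing within-person differences between COPD and controls would be exactly the contrast needed. But the sentence describes a comparison of modes, not of populations, and no other sentence supplies the contrast or a criterion for absence. The mismatch between hypothesis and stated analysis therefore stands, while how the result would be read remains an inference.

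A reader might also take one half as the typical chance of a misleading result. That figure needs a moderate shared effect and all 30 patients against exactly 11 controls, and is close to the maximum. The acute phase is sized at 11 and 11, where the chance never exceeds 25%, and 11 controls is a required number rather than a cap. At the plan's own 11 points and SD 9 the chance is only 4–5%.

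Nor would the whole mechanism rest on one p-value below 0.05 and another above it. Ventilation, oxygen uptake, heart rate, cardiac output and dyspnea are measured directly during the exercises.

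Finally, this is a condensed article, and an interaction term or margin may appear in a fuller plan. That is fair as to detail. But the article does fix a method for this comparison, and that method does not answer the hypothesis it states.

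**Conclusion.** The point holds as a mismatch between the third hypothesis and the stated analysis. T-tests of single versus two limb test neither the difference in mode effect between COPD and controls nor its absence in controls. How often this would mislead depends on the true effect, on the unstated meaning of the SD of 9 and on how many patients' acute visits are analysed. It ranges from negligible (0.3%) to about one half. The calculation assumes paired tests within each group, normally distributed differences and the same SD in both groups.

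The correction is worth making but is not critical to the trial. It concerns one secondary acute-phase hypothesis. The primary comparison of 6-minute walking distance between randomized arms is untouched.

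**What to change.** In the Statistics section, state that the within-person single-minus-two-limb difference will be compared between COPD and controls. A linear mixed model with group, mode, group × mode, visit order and a random participant effect does this, using every patient with both acute visits. Base any COPD-specific claim on the group × mode estimate and its 95% CI.

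Report the mode effect in controls with its 95% CI, and do not conclude no difference from non-significance. Draw that conclusion only against a margin that the sponsor states and justifies beforehand for each outcome, and that is smaller than the 11-point relevant difference. The 11-point figure applies to contractile fatigue only, so exercise stimulus needs its own margin. Without a margin, give the interval and stop there. The sponsor should also say what the SD of 9 refers to.

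The cost is a few lines of text and no new data. The drawback is precision. At SD 9 the contrast has a half-width of about 6.4 points (30/11) or 8.0 (11/11), against 2.045 × 9/√30 = 3.4 for the mode effect in 30 patients or 2.228 × 9/√11 = 6.0 in 11. The disease-specific claim will be harder to make. The wording should be settled before the acute data are analysed.
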